### Primary outcome

The primary outcome is the change in WMH volume based on brain MRI measurements.

### Secondary outcomes

Secondary outcomes include changes of DTI-derived measures, blood biomarker quantifications, in neuropsychological test results over time, novel cerebral ischemic events, myocardial infarction, the clinical disease course as marked by the modified Rankin Scale score (mRS) and quality of life upon 12 months.

### Post-mortem study outcomes

As part of a translational approach, study participants will be asked for a post-mortem donation of their brain for scientific purposes. Outcomes of such postmortem studies include (i) routine neuropathological diagnostics including staging of neurodegenerative changes, (ii) microangiopathy classification and scoring including arterio- and arteriolosclerosis, blood-brain-barrier disturbances, glio-neuronal changes, WMH-related WM pathology, string vessels, vascular bagging, and vascular beta-amyloid (Aβ) accumulation, as well as (iii) size, type (ischemic / hemorrhagic), and location of territorial infarcts, microinfarcts, microbleeds, lacunes, and superficial siderosis.

## Methods

### Participants

#### Study design

The study is a registered (DRKS00038936; date of registration 01.02.2026) investigator-initiated single-center, prospective, observational study with an expected total study duration of 3 years.

The study is conducted at the University Hospital of Ulm, Ulm, Germany. As a tertiary care hospital in southern-central Germany, it serves large parts of southeastern Baden-Württemberg, as well as adjacent regions in Western Bavaria. Participants are recruited at the stroke unit, the normal wards of the Department of Neurology, and neurological outpatients clinics. Patient recruitment started in March 2026. Prior, we conducted a pilot trial, for which recruitment begun in March 2023 with the last patient visit of 29 completely followed-up patients in May 2026 (unpublished data).

At the Department of Neurology, University Hospital Ulm, we treat about 1000 patients with ischemic stroke/transient ischemic attack per year. In approximately one fifth of such cases (*n* = 200), we anticipate a microangiopathic stroke etiology, as confirmed by MRI findings. A territorial stroke etiology is expected with a similar frequency. Furthermore, the neurological clinic annually manages several hundred patients with CSVD, but without evidence of recent cerebral ischemia.

### Eligibility criteria

Patients are eligible as participants if (a) their age is ≥ 18 years and if (b) brain MRI provides evidence of CSVD, defined as WMH (Fazekas grade 1–3). Patients with Fazekas grade 1 will be included as well to cover all different stages of CSVD and because even a mild lesion load has been linked to neurocognitive impairment [21]. In case of uncertainty about the aetiology of WMH, diagnostics to rule out inflammatory diseases or genetic small vessel diseases are planned. Furthermore, (c) patients must be assigned to one of the following groups based on MRI findings: Group 1: CSVD without evidence of an acute ischemic stroke, Group 2: CSVD with acute lacunar ischemic stroke, defined as singular diffusion-weighted imaging (DWI)-hyperintense, apparent diffusion coefficient (ADC)-hypointense lesion on brain MRI with a diameter of maximum of 2.5 cm, or group 3: CSVD with acute territorial ischemic stroke pattern on MRI. All patients must be (d) able to provide written informed consent and (e) have sufficient German language skills to understand study procedures and assessments. The requirement for sufficient German language skills is necessary to ensure valid neuropsychological assessments. However, this criterion may introduce selection bias and may limit the generalizability of the study findings.

Inclusion criteria are as follows:

Age ≥ 18 years.Evidence of CSVD on brain MRI, defined as the presence of WMH (Fazekas grade 1–3).Assignment to one of the defined study groups based on MRI findings.Ability to provide written informed consent.Sufficient German language skills.

Exclusion criteria are as follows:

Alternative plausible causes of WMH other than CSVD.Known neurodegenerative diseases.Acute or recent traumatic brain injury.Contraindications to MRI.Pregnancy or breastfeeding.Expected life expectancy of less than one year.Inability to comply with study procedures or follow-up visits.Severe renal insufficiency with an estimated glomerular filtration rate <15 ml/min

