Beyond brain MRI, no clinically established in vivo surrogate marker for CSVD activity currently exists. Blood-based biomarkers represent a promising approach for monitoring longitudinal disease activity and potential regression. Of those, serum neurofilament light chain (NfL) levels seem in particular promising as they have been found to reflect imaging burden and neuropsychological features (processing speed performance) of CSVD in a cross-sectional study including more than 500 patients [14]. Furthermore, temporal changes of serum NfL have been described in a monocenter cohort of 79 patients after a recent small subcortical infarct upon 15 months. Compared to healthy controls, NfL levels were increased shortly after stroke and until 3 months, returning to normal levels after 15 months [15]. New incident ischemic lesions on MRI were reflected by secondary NfL increases [15]. Further results from the Alzheimer’s Disease Neuroimaging Initiative (ADNI) showed that plasma NfL correlated positively with CSVD severity, and with the presence of cerebral microbleeds (CMBs) and lacunes [16]. With higher the changes in plasma-NfL were over time, the CSVD burden and WMH increased upon a mean follow-up of 27 months in 378 patients [16]. These findings imply an additional value of blood NfL measurements for disease monitoring, which may be complementary to brain MRI.

In a monocenter, prospective registry, serum GFAP correlated with verbal fluency, visuomotor and executive functions in patients with CSVD [17]. Lately, in a follow-up study over 12 months, vascular endothelial growth factor (VEGF) levels in the blood were associated with incident brain lesions in a longitudinal study [18]. Beyond that, such biomarkers have demonstrated substantial diagnostic and longitudinal value in other neurological disorders, including multiple sclerosis and neurodegenerative diseases [19, 20].

The present prospective cohort study builds upon a previously conducted single-center pilot study by our group (local Ethics approval no. 343/22), which demonstrated the feasibility of longitudinal biomarker measurements in patients with CSVD and provided preliminary evidence supporting associations between biomarker dynamics and MRI-detected CSVD progression.

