### Parameters

In participants with known CSVD, age at disease onset and past brain MRI results will be collected. For each patient, at each visit, the following clinical parameters will be recorded: (1) current global or focal neurological symptoms (e.g. subjectively evident memory disorders, gait disorders, dysarthria, focal motor or sensory symptoms, bladder dysfunction, dizziness/vertigo), those symptoms are summed up using the National Institutes of Health Stroke Scale (NIHSS) is a standardized 15-item neurological examination tool used by healthcare professionals to quantify acute stroke severity and monitor neurological changes and the modified Rankin Scale (mRS), a 6-point scale for measuring the degree of disability or dependence in the daily activities (2) current blood pressure, heart rate, peripheral Sp02 saturation, (3) height and body weight to calculate the body mass index.

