### Biosamples

At all scheduled study visits, venous blood samples will be collected, processed, aliquoted, and stored in the biobank of the Department of Neurology according to established standard operating procedures. Laboratory analyses include a comprehensive panel of vascular, metabolic, inflammatory, and neurodegeneration-related parameters. Vascular and metabolic markers comprise lipid parameters (Low- and high-Density Lipoprotein (LDL, HDL), cholesterol, triglycerides, and lipoprotein(a)) as well as markers of glucose metabolism, including insulin and glycated hemoglobin (HbA1c). Cardiac biomarkers (troponin I or T) at baseline in groups 2 and 3 and inflammatory markers, including high-sensitivity C-reactive protein, interleukin-6, and interleukin-1 alpha, are assessed to characterize systemic vascular and inflammatory status [27].In addition, blood-based biomarkers reflecting central nervous system injury are analyzed, e.g. GFAP as a marker of glial activation, neurofilament light chain (NfL) as a marker of axonal damage, phosphorylated tau 217 (pTau217) as an exploratory neurodegeneration-related biomarker, and beta-synuclein as an exploratory synaptic marker.

CSF samples obtained as part of routine clinical care and based on clinical indication (e.g. to exclude inflammation or vasculitis) will be used for biomarker analyses, including total tau protein, phosphorylated tau, and amyloid-β1–42. In addition, endothelial cell–related biomarkers, including endothelin-1 and vascular cell adhesion molecule-1 (VCAM-1), are analyzed to capture endothelial dysfunction associated with cerebral small vessel disease [28, 29].

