### Benefit–risk assessment

Participation in the study is associated with low additional risks. The potential risks are minimal and mainly related to blood sampling and MRI examinations [2]. The MRI examinations are conducted without contrast agents, and all participants are comprehensively informed about potential discomforts and contraindications during the consent process.

There is no direct therapeutic benefit for participants. However, participants and/or their treating physicians may receive additional diagnostic information regarding disease progression and corresponding clinical counseling.

Given the minimal procedural risks and the substantial scientific value of identifying blood-based biomarkers for CSVD activity and progression, the overall benefit–risk ratio of the study is considered favorable.

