### Statistical methods

#### Methods of analyses

The statistical analysis will be purely descriptive. Categorical variables will be summarized using absolute and relative frequencies, while continuous variables will be described using the mean and standard deviation or the median, interquartile range, and minimum and maximum values, as appropriate. Group differences will be assessed according to the measurement scale and distribution using the t-test or Wilcoxon signed rank test for continuous variables, and the chi-square test or Fisher’s exact test for categorical variables. To investigate temporal changes in parameters, individual slopes will first be estimated using linear mixed-effects models with random intercepts for participants to account for within-subject correlation. They will be subsequently compared between groups. In a further step, notable group differences will be explored using appropriate regression methods (linear regression, logistic regression, and, if applicable, mixed-effects models).

Differences in follow-up imaging with regard to the number and volume of radiological markers of CSVD will be analyzed using the Wilcoxon rank-sum test. Associations between continuous variables will be examined using scatter plots; where appropriate, Pearson or Spearman correlation coefficients will be calculated. Longitudinal data (e.g. the course of one or more biomarkers) will be illustrated by scatter/dotted plots and spaghetti plots, as appropriate. All statistical tests will be conducted using a two-sided significance level of α = 0.05. No adjustment for multiple testing will be performed. Given the exploratory nature of the study, all statistical test results will be interpreted as hypothesis-generating rather than confirmatory. Statistical analyses will be performed with R, The R Project for Statistical Computing with the latest version available (currently 4.5.3).

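### Marker–WMH and marker–cognition links are planned as crude correlations, which cannot separate CSVD activity from undiagnosed neurodegeneration, although pTau217 is measured at every visit

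*Protocol article*

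**What the plan says.** The objectives at the end of the Introduction put first the search for one blood marker, or a set, that identifies progression of CSVD. The Introduction also states that "such biomarkers have demonstrated substantial diagnostic and longitudinal value in other neurological disorders, including multiple sclerosis and neurodegenerative diseases".

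Eligibility criteria exclude "Known neurodegenerative diseases" and "Severe renal insufficiency with an estimated glomerular filtration rate <15 ml/min". They also exclude "Alternative plausible causes of WMH other than CSVD" and recent brain trauma, and they plan work-up for inflammatory or genetic disease where the origin of the WMH is uncertain.

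Biosamples lists GFAP, NfL, beta-synuclein and "phosphorylated tau 217 (pTau217) as an exploratory neurodegeneration-related biomarker". Blood is drawn at all scheduled visits, and Table 2 marks biomarkers at months 0, 3, 6 and 12. Parameters records "height and body weight to calculate the body mass index" at each visit. Neither creatinine nor eGFR is named in the laboratory panel.

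Methods of analyses states: "Associations between continuous variables will be examined using scatter plots; where appropriate, Pearson or Spearman correlation coefficients will be calculated". Regression and mixed models are named for temporal slopes and for exploring notable group differences. No covariate is named. All tests are two-sided at 0.05 without multiplicity adjustment, and results are to be read as hypothesis-generating.

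**The concern.** The first objective depends on specificity: a useful marker must follow CSVD, not just brain injury from any source. By the article's own account the candidate markers are not specific. The exclusion of neurodegenerative disease works only where a diagnosis already exists, and no biomarker, imaging or cognitive threshold is given to find silent disease.

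If undiagnosed neurodegeneration raises a marker and also goes with faster WMH growth or poorer cognition, a crude correlation will appear without any direct link to CSVD activity. That is a systematic error. It would carry into any later study built on the chosen marker. The variable best placed to examine it, pTau217, is already in the sampling plan but is treated only as one more candidate marker.

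**Working it through.** **The plan's own figures.** The Sample size section gives sensitivity for WMH change only. Those figures reproduce under the normal approximation with 1.96 + 0.84 = 2.80:
- within group: 2.80/√60 = 0.36 and 2.80/√45 = 0.42
- between groups: 2.80 × √(2/60) = 0.51 and 2.80 × √(2/45) = 0.59

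No figure is given for a marker–WMH correlation, so nothing stated there changes.

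**Inputs for the illustration.**
- From the documents: at most 180 patients with 25% drop-out, so 180 × 0.75 = 135 completers (45 per group); two-sided α = 0.05.
- Assumed, because the documents give no value: a shared factor correlates *a* = 0.3–0.5 with the marker and *b* = 0.1–0.3 with WMH change, and marker and WMH change have no direct link.

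**Step 1, crude correlation.** With no direct link, r = a × b. The range is 0.3 × 0.1 = 0.03 to 0.5 × 0.3 = 0.15.

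**Step 2, chance of a nominally significant result.** By Fisher z, the shift is δ = artanh(r) × √(n − 3), and the rejection probability is P(Z > 1.96 − δ) + P(Z < −1.96 − δ). With n = 135, √132 = 11.49.

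| a | b | r | δ | Rejection, n = 135 |
|---|---|---|---|---|
| 0.3 | 0.1 | 0.03 | 0.34 | 6.4% |
| 0.3 | 0.3 | 0.09 | 1.04 | 17.9% |
| 0.4 | 0.3 | 0.12 | 1.39 | 28.3% |
| 0.5 | 0.3 | 0.15 | 1.74 | 41.2% |

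Within one group of 45 (√42 = 6.48), the two ends of the range are 5.4% and 16.5%.

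**Step 3, what adjustment does.** The numerator of the partial correlation is r − a × b. It is zero here, so rejection returns to about 5%, provided the factor is well measured and correctly modelled. If pTau217 captures undiagnosed neurodegeneration only in part, some bias remains.

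**Step 4, what adjustment can cost.** If pTau217 shares CSVD signal with the marker, the variance of the marker's coefficient is inflated by 1/(1 − r²), where r is the pTau217–marker correlation: 1/(1 − 0.09) = 1.10 at r = 0.3 and 1/(1 − 0.25) = 1.33 at r = 0.5. In that case 135 patients carry the information of about 135 × 0.91 = 123, or 135 × 0.75 = 101. If the pTau217-related part of the marker is pure noise for WMH change, adjustment gains precision instead. The documents do not show which case applies.

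**The case against.** The strongest reply is that this is a journal article without its analysis plan, that covariate lists usually sit in that plan, and that the correlation sentence covers continuous variables in general without calling itself the only marker–WMH analysis. This stands as far as a bare missing list goes. It does not dispose of the point, because the article names a method for such associations, that method is unadjusted, and the regression step is tied to group differences.

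A second reply is that results are hypothesis-generating, that other causes of WMH and recent trauma are excluded, and that autopsy will stage neurodegenerative change. These are real but partial safeguards. The label deals with chance findings, not with systematic confounding. The other exclusions do not detect silent neurodegeneration. Autopsy reaches only consenting participants who die.

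A reader might also infer that kidney function and BMI are collected and then wrongly ignored, or that the eGFR rule exists to protect marker levels and is set too low for that. The documents do not support this. No passage says that renal function or BMI shifts NfL or GFAP. No reason is given for the renal threshold, and the statement "The MRI examinations are conducted without contrast agents" makes a marker-related purpose conceivable but does not show it. Renal function appears only as an entry criterion, not as serial data. Nor is pTau217 left unanalysed: it is itself an exploratory marker, and only its use as an adjuster is missing.

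**Conclusion.** The point holds for neurodegeneration. The stated association analysis is crude, the exclusion covers known disease only, the article concedes that the markers are non-specific, and a measured variable that could help separate the sources has no role as an adjuster.

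The size is not known. The 6–41% range rests wholly on assumed correlations. Its low end is close to the nominal 5%, and confounding also requires a link between neurodegeneration and WMH change or cognition that the documents do not quantify. It would go too far to conclude that NfL or GFAP will be wrongly named as CSVD markers. What can be said is that the planned analysis could not show whether they had been. This is a worthwhile and inexpensive improvement to an exploratory analysis. It gives no reason to alter eligibility.

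**What to change.** Keep the scatter plots and crude correlations. Add to Methods of analyses:

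1. A partial-correlation or regression analysis of NfL, GFAP and beta-synuclein against WMH change and against cognition, adjusted for age (eligibility runs from 18 years upward) and pTau217, reported beside the crude result.
2. As a sensitivity analysis, the lead association repeated across pTau217 levels.
3. A statement of which visit's pTau217 value is used, with the caveat that an effect of the acute stroke on it cannot be excluded. The Introduction reports NfL raised until 3 months after a small subcortical infarct and gives no time course for pTau217, so the month-3 value cannot simply be taken as free of stroke effects.
4. Renal function and BMI as optional covariates only. Using renal function at each visit would first require it to be recorded with the blood samples.

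The cost is a short paragraph, two degrees of freedom for age and pTau217 (more with the optional terms), and possible loss of precision if pTau217 shares CSVD signal. Nine participants had been enrolled by 11 June 2026, so the addition can still be fixed long before analysis.

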### Informed consent

All participants need to give their written informed consent to participate. The study is conducted according to the Declaration of Helsinki, its original version and its latter amendments with the latest amendment of 2024.

#### Sample size

We aim to include 60 patients in the three study groups, resulting in a maximum total number of 180 patients. We expect a drop-out proportion of 25%, relating to difficulties of mobility and morbidity for adherence in follow-up visits of patients with territorial brain ischemia in particular and considering the rural area surrounding the region of Ulm, Baden-Württemberg, Germany. The calculation of sample size is not based on a confirmatory study aim, but is exploratory and mirrors our experiences made in the pilot study of the recruitment that can be expected and delivered in our clinical setting in Ulm.

As an illustration of sensitivity: in a pilot subset (unpublished data) with paired manual WMH volumetry (17 patients), the mean 12-month WMH volume change was 5.30 mL (SD 6.03; standardized within-subject effect d_z ≈ 0.88). A within-group comparison detects a change of this magnitude at ~ 80% power (two-sided α = 0.05) in ~ 10 patients per group. With 60 patients per group (≈ 45 completing follow-up after the anticipated 25% drop-out), the planned cohort is sensitive to within-subject WMH changes as small as d_z ≈ 0.36 (at 60 per group) to 0.42 (at 45 per group), i.e. ≈ 2.2–2.5 mL, well below the 5.30 mL observed in the pilot data, and, for exploratory between-group comparisons, to standardized differences of d ≈ 0.51 (at 60 per group) to 0.59 (at 45 per group), a ≈ 3.1–3.6 mL difference in WMH change between groups.

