### Recruitment

The recruitment is carried out by a designated study team of the Department of Neurology, University Hospital Ulm, Germany, during the in-patient stay of patients eligible for participation in Groups 2 and 3. Patients with CSVD without a current stroke are recruited at our specialized outpatient clinic for CSVD and cerebrovascular diseases. As of June 11th, 2026 6 male patients and 3 female patient were enrolled. Of those, 5 (56%) presented with acute territorial stroke and were recruited in Group 3, 3 had a lacunar stroke and were assigned to group 2 (33%) and one further participant without acute stroke was recruited into group 1 (11%). The median age was 68 years with a minimum of 52 and a maximum of 85 years.

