To account for scanner differences between acquisitions, WMH segmentation will be performed using a FLAIR-only automated in-house pipeline based on the half-Gaussian mixture model described by Igwe et al. [25], which models log-transformed above-mode FLAIR intensities as a two-component mixture: a half-Gaussian for normal-appearing white matter and a full Gaussian for WMH, with all five parameters estimated via expectation-maximization. The original method was validated on a single scanner and timepoint; we extend it to longitudinal cross-scanner comparison by fitting the HGMM independently per timepoint on a shared white matter territory (intersection of both timepoints’ white matter labels), with a two-pass refinement that excludes candidate WMH from the fit pool to tighten the normal-appearing white matter model. Longitudinal change is estimated through paired voxel-wise contrast at the TP1 lesion boundary, corrected for scanner offset (estimated from stable white matter) and blur mismatch, rather than by subtracting two independent segmentations. Anatomical false positives are removed through automated exclusion. Acute DWI lesions identified on the baseline MRI were registered to FLAIR space andexcluded from the WMH volume calculations at baseline, 6-month, and 12-month follow-up. This procedure ensured that longitudinal WMH measurements represented chronic white matter disease burden, independent of the baseline acute infarct.

In the pilot cohort, baseline and follow-up FLAIR were acquired on different scanners and protocols, so standard endpoint WMH segmentation could not reliably separate true lesion change from scanner-induced contrast shifts. We therefore used a scanner-aware longitudinal pipeline designed to identify the FLAIR change as biological progression rather than scanner change artifacts. Since the prospective cohort is acquired on a stable, harmonized protocol, Deep WMH and Multi-site Auto-segmentation and Registration of Subcortical White Matter Hyperintensities (MARS)-WMH-derived segmentation will additionally be evaluated, with agreement to the manual reference quantified by Dice similarity coefficient and ICC.

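### In the Sample size section, 10 patients give about 70% power under a paired t-test, not about 80%, and the mL figures rest on a 17-patient pilot benchmark not reconciled with the pilot's scanner change

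*Protocol article*

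**What the plan says.** The Sample size section sets 60 patients per group (at most 180), expects 25% drop-out and so about 45 completers per group. It calls the size exploratory and ties it to recruitment experience from the pilot. It then illustrates sensitivity from a pilot subset "with paired manual WMH volumetry (17 patients"), in which "the mean 12-month WMH volume change was 5.30 mL (SD 6.03; standardized within-subject effect d_z ≈ 0.88"). From this it states: "A within-group comparison detects a change of this magnitude at" the level given as "at ~ 80% power (two-sided α = 0.05) in ~ 10 patients per group". For 60 and 45 per group it gives detectable within-subject d_z of 0.36 and 0.42 (2.2–2.5 mL) and between-group d of 0.51 and 0.59 (3.1–3.6 mL). It describes the within-subject values as "well below the 5.30 mL observed in the pilot data".

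The Postprocessing section says of the same pilot that "baseline and follow-up FLAIR were acquired on different scanners and protocols, so standard endpoint WMH segmentation could not reliably separate true lesion change" from contrast shifts caused by the scanner. It reports that a scanner-aware pipeline was therefore used. That pipeline estimates change by a paired voxel contrast at the baseline lesion boundary, not by subtracting one segmentation from another. The Statistical methods section names the t-test or the Wilcoxon signed rank test for continuous variables, at two-sided α = 0.05.

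**The concern.** Ten patients is a sample at which the normal approximation to the t-test is poor, so the stated pairing of about 10 patients with about 80% power looked too favourable.

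The larger question is the benchmark. The SD of 6.03 mL converts every standardised effect in the paragraph into mL, and the mean of 5.30 mL is the yardstick for the reassurance about detectable change. Both come from manual volumes on scan pairs whose scanner and protocol changed between visits. The Sample size section mentions neither that change nor any figure from the scanner-aware pipeline, and it gives no interval around a 17-patient estimate. WMH volume change is the primary outcome, so a reader will take these mL values as the study's sensitivity for its main question.

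**Working it through.** **Inputs.** From Sample size: mean 5.30 mL, SD 6.03 mL, n = 17, two-sided α = 0.05, power 80%, 60 and 45 per group. d_z = 5.30/6.03 = 0.879.

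**1. The plan's own figures, by normal approximation.**
- Patients needed: n = ((1.960 + 0.842)/0.879)² = 10.16.
- Power at n = 10: Φ(0.879·√10 − 1.960) = 79.4%.
- Detectable d_z = 2.802/√n: 0.362 at 60 and 0.418 at 45. Multiplied by 6.03, this is 2.18 and 2.52 mL.
- Detectable d = 2.802·√(2/n): 0.511 at 60 and 0.591 at 45, or 3.08 and 3.56 mL.

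Every stated figure reproduces with this formula.

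**2. The same quantities for the t-test** (noncentral t, two-sided, noncentrality d_z·√n, n − 1 degrees of freedom).

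| n | Power at d_z 0.879 |
|---|---|
| 10 | 69.7% |
| 11 | 74.8% |
| 12 | 79.1% |
| 13 | 82.8% |

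At the planned sizes the change is negligible:

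| | Normal approximation | t-test | t-test, in mL at SD 6.03 |
|---|---|---|---|
| d_z, 60 per group | 0.362 | 0.368 | 2.2 |
| d_z, 45 per group | 0.418 | 0.427 | 2.6 |
| d, 60 per group | 0.511 | 0.516 | 3.1 |
| d, 45 per group | 0.591 | 0.597 | 3.6 |

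**3. Precision of the pilot benchmark, taken at face value.**
- Mean: 5.30 ± 2.12 × 6.03/√17 = 5.30 ± 3.10, so the 95% CI is 2.2 to 8.4 mL.
- SD: √(16 × 6.03²/28.85) to √(16 × 6.03²/6.91), so the 95% CI is 4.5 to 9.2 mL.
- d_z: 95% CI 0.31 to 1.43 (noncentral t). At d_z = 0.31 the power is 53% with 45 patients and 66% with 60.
- Detectable change at 45 per group over the SD interval: within group 0.427 × 4.49 to 0.427 × 9.18 = 1.9 to 3.9 mL; between groups 0.597 × 4.49 to 0.597 × 9.18 = 2.7 to 5.5 mL.

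The lower limit for the mean, 2.2 mL, coincides with the low end of the stated detectable 2.2–2.5 mL.

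**4. The two sections side by side.** Sample size uses paired manual volumes from the pilot. Postprocessing says the pilot's two scans differed in scanner and protocol, that standard endpoint segmentation was unreliable for change for this reason, and that change is to be estimated by another method. The Fig. 1 caption shows pilot manual segmentation done separately at each time point, with a white-matter intensity mode of 383 at baseline and 178 at follow-up in the example. The benchmark is therefore a manual measure of change on scan pairs of the kind the protocol warns about, and it is not the change measure planned for the cohort.

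**The case against.** The strongest reply is that the paragraph is offered only as an illustration in an exploratory study whose size rests on recruitment, and whose tests are all labelled hypothesis-generating. Its numbers follow from a standard formula, both 10 and 80% are marked approximate, and no planned group size depends on that sentence. All of this is right. It limits the weight of the power error but does not make 70% into 80% at n = 10. The Sample size section does not name the test behind the figure. The paired t-test is the natural reading of a d_z calculation and belongs to the family named under Statistical methods.

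On the benchmark, a reader might infer that the protocol itself declares 5.30 mL to be scanner artefact. It does not. The Postprocessing statement concerns standard endpoint segmentation and does not name manual volumetry, and manual segmentation is treated there as the reference. A reader might also infer that the benchmark is too high. The documents give no direction: scanner shift could raise or lower the mean. Added scanner noise could inflate the SD, which would make the mL thresholds conservative for a cohort that the protocol expects to be scanned on a stable protocol. The d_z and d thresholds do not use the pilot at all. The comparison with 5.30 mL is also literally true of the point estimate. What remains is that one section relies on pilot volumes without mentioning a limitation that another section describes, and without an interval.

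Two further readings are tempting. One is that this paragraph is the only justification of the sample size; the section itself gives recruitment experience as the basis. The other is that accrual shows 45–60 per group cannot be reached. By 11 June 2026, after a March start, "6 male patients and 3 female patient were enrolled", which is 2.7–3.8 per month, against 180/24 = 7.5 per month if intake lasts 24 months. But the 24 months is an assumption, nine patients in the opening months are few, 180 is a maximum, and the Study design section describes a large source population. The pilot record, "recruitment begun in March 2023 with the last patient visit of 29 completely followed-up patients in May 2026", runs from first recruitment to last visit and counts completers only, so it is not an accrual rate. Slow early accrual is at most a provisional feasibility note.

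**Conclusion.** The point holds in two parts.

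- **Power figure.** For a two-sided paired t-test at d_z 0.88, 10 patients give about 70% power, some 10 percentage points below the stated level; 12 give 79% and 13 give 83%. This assumes roughly normal changes. The standardised thresholds at 45–60 per group stand, moving by only about 0.01.
- **Benchmark.** The mL values and the comparison with 5.30 mL rest on an unreconciled pilot measure. That scanner change affected it is a reasonable inference, with neither direction nor size known. Independently of that, the 95% CI of 2.2–8.4 mL for the mean means the comparison is secure only for the point estimate. The 95% CI of 4.5–9.2 mL for the SD leaves the detectable differences in mL much less certain than printed.

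The planned sample size is not shown to be wrong. The illustration should be corrected because it puts specific numbers on the primary outcome.

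**What to change.** 1. Replace about 10 patients with 12 to 13, or keep 10 and state about 70% power, and name the test used.
2. Recompute the mean and SD of 12-month change in the same 17 pilot patients with the scanner-aware pipeline. Report both with 95% confidence intervals, next to the manual values if those are kept, and say how the manual values relate to the scanner change described under Postprocessing.
3. Redo the conversions from d_z and d to mL with the recomputed SD and show the range over its interval.
4. Drop the statement that detectable changes lie well under the pilot change, or qualify it with the interval around that change.

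The cost is a small re-analysis of existing scan pairs with an existing pipeline, and a few sentences of text. The stated sensitivity may become less favourable. Nothing in the design, schedule or target numbers has to change.
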